### Data analysis

Descriptive statistics (e.g. means, standard deviations/variances, medians with inter-quartile ranges, and frequency distributions) will be used to describe participant demographic characteristics. The chi-squared statistic test will be used for categorical variables whereas T-test (parametric) or Wilcoxon rank sum test (non-parametric) will be applied for continuous variables. Transformations of outcome variables will be explored and performed if appropriate. Multivariate logistic regression models will be performed to examine associations between covariates. Since data is collected on one subject over time, the data will be treated as longitudinal data. Generalized linear mixed effect models will be fitted to determine associations of interest with time and intervention effects included as fixed effects and allowing for subject-specific random effects. Alternatively, generalized estimating equations can be used to account for any correlations of repeated data measures, when assessing determinants of PrEP adherence at time points provided we have balanced data with ignorable missing patterns. Time-to-event analysis will be conducted using Kaplan-Meier plots. To determine possible associations with covariates, a Cox-proportional hazard will be used. If the proportional hazard assumption does not hold, an accelerated failure time model will be used. Missing data due to loss to follow-up is inadvertent and inevitable. The extent of missing data will be assessed in the primary analysis. The primary analysis will be conducted under the assumption of data Missing at Random (MAR). As such, longitudinal likelihood-based data analysis, utilizing all the observed pre-deviation data from each participant will be employed. Thereafter, multiple imputation (MI) method will be employed under the primary MAR assumption, and Rubin’s rule will be followed to combine results. Sensitivity to deviation from the MAR assumption will be investigated. Intention to treat (ITT) assessment with complete case approaches where necessary will be implemented in cases of non-adherence to randomization assignment. Depending on the extent of non-adherence, the “as treated (AT)” approaches may be employed to analyse participants according to the intervention received regardless to their randomized allocation. A marker of level of adherence can also be included in the models. Patterns of PrEP use will be identified using latent class models or clustering techniques and the association of factors with these latent classes will be examined using multinomial logistic regression modelling. For all statistical investigations, tests for significance will be two-tailed. Analyses will be conducted using STATA 13.0 or R version 4.

Qualitative data analyses of participant and staff IDIs, CAB FGDs, CMEs, and staff SEPs will be conducted using a constant comparison approach guided by the study IMB framework. Data and results will be triangulated using matrices to refine findings [61]. Transcripts will be analysed by the qualitative research team, with results presented to study leadership for review and to guide additional analyses. Socio-behavioural factors and contextual (urban v. rural) influences influencing young women’s action plans for PrEP uptake and adherence will be used to create risk and adherence profiles to inform eventual intervention tailoring and implementation.

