### Intervention design and adherence support activities

#### Description of the intervention

The intervention arms were developed using the Information-Motivation-Behavioural Skills Model of Behaviour Change (IMB) [42, 43]; the IMB model has been used extensively to improve medication adherence, including for ART [42–44] and daily contraceptives [45]. Intervention arms will incorporate content from the evidence-based intervention Life Steps [46], as well as from the HIV Prevention Trials Network 082 study [47] and the 3Ps for Prevention open-label PrEP demonstration study [48]. Using standardized manuals, adherence support interventions will be delivered in either a group (Arm 1) or one-on-one individual (Arm 2) sessions. Participants randomized to intervention arms will be seen by adherence counsellors monthly for 24 months at a fixed community-based site.

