### Sample size and power calculations

A sample size was calculated to have 80% power to detect differences in the proportion of participants adhering to PrEP among the three study arms (Aim 2) using the chi-square test for independence with two degrees of freedom, with an alpha of 0.05, and assuming an attrition rate of 10% for those who (1) withdraw voluntarily from the study, (2) initiate on PrEP but withdraw due to adverse events (e.g. hepatic or renal abnormalities), or (3) become ineligible for PrEP (e.g. seroconvert). The effect size estimate was informed by prior experience from the field, where an effect size of 0.30 has been found between ART clients receiving some adherence support and those receiving none. However, we use a more conservative effect size of 0.15, to account for the fact that adherence support may not lead to the same gains in adherence among HIV-negative PrEP clients as it does with HIV-positive ART clients. The sample size was calculated to be 160 per arm (480 total).

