## Discussion

The Community PrEP Study is an innovative, mixed-methods study that aims to provide robust insights into (1) the acceptability, feasibility, and uptake of PrEP as a methods for HIV prevention by AGYW when delivered through CBCT platforms, (2) community-based prevention-effective adherence support for AGYW, and (3) the cost-effectiveness of such community-based approaches to delivering PrEP services. Numerous barriers have been described that delay or block AGYW from accessing clinic-based health services, especially reproductive health and HIV testing and prevention services. Consequently, reaching AGYW at scale with HIV prevention services requires delivery platforms outside of clinic-based facilities. Our use of community-based platforms to increase AGYW’s access to PrEP and provide same-day initiation is novel. If found to be acceptable and feasible, CBCT platforms can be used to target PrEP services to other at-risk and key populations.

Recent work has highlighted that positive peer support [63–65] and cognitive-behavioural problem-solving [46, 66] consistently improve medication adherence among adults and adolescents. Peer norms play an important role in shaping behaviours, especially for adolescents and young people [67, 68], and community-based approaches that build on peer support may have a strong influence on young women. Our group-based health clubs are highly innovative because they will (1) draw on peer support and cohesion to promote prevention-effective adherence to PrEP to prevent HIV infection, (2) provide a forum for adherence support outside the formal clinic environment, (3) create a positive group norm around the use of PrEP, and (4) provide a space to build social relationships and bonds with other AGYW who are using PrEP. If found to be effective, our prevention-effective adherence support interventions may be tailor for other at-risk groups and communities. Finally, given South Africa’s embrace of group-based ART adherence programmes [69, 70], our adherence support intervention will be well positioned to be integrated into South Africa’s current adherence support strategies.

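### Arm 1 is delivered in health clubs, but the stated models and the sample size treat its women as independent, so tests involving Arm 1 exceed 5% type I error whenever outcomes correlate within clubs

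*Protocol article*

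**What the plan says.** All from the protocol article.

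- **Delivery** (Description of the intervention): "adherence support interventions will be delivered in either a group (Arm 1) or one-on-one individual (Arm 2) sessions", monthly for 24 months. Under Control, the third arm gets refills and passive support, with no adherence session.
- **Mechanism** (Discussion): the health clubs are intended to use peer support and cohesion and to "create a positive group norm around the use of PrEP".
- **Sample size** (Sample size and power calculations): "80% power to detect differences in the proportion of participants adhering to PrEP among the three study arms", found "using the chi-square test for independence with two degrees of freedom, with an alpha of 0.05", with 10% attrition. On the effect, "we use a more conservative effect size of 0.15". The result is 160 per arm, 480 in total. No club size, ICC or design effect is mentioned.
- **Analysis** (Data analysis): generalised linear mixed models "with time and intervention effects included as fixed effects and allowing for subject-specific random effects". The GEE alternative is introduced to handle correlation between repeated measurements. No term refers to the club.

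**The concern.** This is a partially nested design: one arm is grouped after randomisation and the other two are not. If the clubs work as the Discussion intends, women in the same club will tend to adhere, or not, together. A subject random effect captures correlation between visits of one woman. It does not capture correlation between different women in one club.

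Analysed as stated, the Arm 1 mean would be credited with more information than it holds. Standard errors for Arm 1 v control and Arm 1 v Arm 2 would be too small, and the three-arm test would reject too often. The Discussion presents the group model as well placed for integration into national adherence strategies, so a false positive here would matter.

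**Working it through.** **1. Reproduce the plan's figure.** Reading 0.15 as Cohen's w, with 2 df, alpha 0.05 and 80% power, the required noncentrality is 9.635.

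- N = 9.635 / 0.15² = 428.2, so 429 (143 per arm).
- With 10% attrition: 429 / 0.9 = 477, rounded to 160 per arm = 480.
- Evaluable after attrition: 480 × 0.9 = 432, or 144 per arm. Noncentrality 432 × 0.0225 = 9.72, power 80.4%.

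So 480 is the independence figure, with no allowance for clubs and almost no slack.

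**2. Assumed inputs.** The readable text gives neither club size nor ICC. Assumed: m = 6 to 12 women per club, ICC = 0.01 to 0.10.

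**3. Type I error of Arm 1 v control when clubs are ignored.**

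- Design effect in Arm 1 only: DE = 1 + (m − 1) × ICC.
- True over assumed standard error: r = √((DE + 1)/2).
- Type I error = 2 × (1 − Φ(1.96/r)).

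For m = 10 and ICC 0.05: DE = 1 + 9 × 0.05 = 1.45; r = √(2.45/2) = 1.107; 1.96/1.107 = 1.771; type I error 7.7%.

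**4. Power of the stated 2-df test once clubs are allowed for.** Replace n₁ = 144 by 144/DE. If one arm differs from the other two by a standardised d, then 9.72 = d² × 144 × 288/432, so d² = 0.10125. For m = 10 and ICC 0.05, n₁ = 144/1.45 = 99.3 and the total is 387.3.

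- Both interventions equally better than control: 0.10125 × 144 × 243.3/387.3 = 9.16, power 77.8%.
- Only Arm 1 better: 0.10125 × 99.3 × 288/387.3 = 7.48, power 68.6%.

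**5. Over the assumed range.**

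| m | ICC | DE | r | Type I error, Arm 1 v control | Power, both work | Power, only Arm 1 works |
|---|---|---|---|---|---|---|
| 6 | 0.01 | 1.05 | 1.012 | 5.3% | 80% | 79% |
| 6 | 0.05 | 1.25 | 1.061 | 6.5% | 79% | 74% |
| 10 | 0.01 | 1.09 | 1.022 | 5.5% | 80% | 78% |
| 10 | 0.05 | 1.45 | 1.107 | 7.7% | 78% | 69% |
| 10 | 0.10 | 1.90 | 1.204 | 10.4% | 76% | 59% |
| 12 | 0.10 | 2.10 | 1.245 | 11.5% | 76% | 55% |

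**6. Check by simulation.** Beta-binomial clustering in Arm 1 only, 144 per arm, 100,000 runs, common proportion 0.3 or 0.5. At m = 10 and ICC 0.05 the unadjusted three-arm test rejects in 7.4% to 7.8% of null trials, and Arm 1 v control in 7.8% to 7.9%. Using Arm 1's effective sample size brings the three-arm test back to about 5%.

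**The case against.** - **The size is assumed.** Neither ICC nor club size is in the readable text, and Table 3, which describes the intervention components, could not be read in the copy available. At ICC 0.01 the inflation is slight (5.3% to 5.6% for 6 to 12 per club). This stands: the direction is clear, the size is not.
- **Clubs are looser than the model.** The Discussion expects small groups to be merged and sessions to be scheduled flexibly. Table 4 anticipates women who never return and women who miss consecutive visits. By intention to treat they count in Arm 1 but share little club experience, which would tend to lower the ICC. This also stands, and it means that membership must be defined before a club term can be fitted.
- **An article condenses.** The full random-effects structure may be in an analysis plan that is not shown. This is a fair caution for the model, but the article does name the random effect and limits its GEE option to repeated measures. It does not help the sample size, which step 1 shows to be the independence figure.
- **Power.** A reader might infer that the stated 80% is plainly wrong, or cite a fall from 77% to 68% for Arm 1 v control (m = 10, ICC 0.05). The documents do not support that reading. The 80% belongs to the three-arm test, and no power is claimed for any pair. For the stated test, the loss is under 3 percentage points in the middle case if both interventions work equally, which is the pattern closest to the Aim 2 hypothesis in Table 1.

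**Conclusion.** The point holds, conditionally. As written, the analysis and the sample size carry no between-club variance for an arm whose mechanism implies it. Type I error is therefore above 5% for Arm 1 contrasts and for the three-arm test whenever the within-club ICC is positive. How far above depends on club size and ICC, which are assumptions here, so it may be trivial or more than double the nominal level.

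Two broader conclusions should not be drawn. Not every comparison is compromised: Arm 2 v control involves no clubs and is untouched. Nor is the 80% power wrong outright: it is correct with no within-club correlation, and the loss otherwise depends on which arms work. Inflated type I error is the main harm; reduced power is what appears once the analysis is made valid.

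**What to change.** **Model.** Use a partially nested mixed model: a random club intercept active in Arm 1 only, in addition to the subject effect, with small-sample degrees of freedom. The correction is needed because clubs are few: 144 evaluable women make 24 clubs of 6 or 12 clubs of 12. The alternative is GEE with variance robust at club level, also corrected for few clubs.

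**Definitions.** Define club as the first club to which a woman was assigned, so that later merging does not redefine the clusters. Treat women in the other two arms, and Arm 1 women never placed in a club, as singletons.

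**Data.** Confirm that a club identifier is captured. The article mentions an attendance check-in but does not say that club membership is recorded. If it is not, it needs to be reconstructed from session records, where these allow.

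**Reporting.** Report the estimated ICC. Restate the 80% as holding only without within-club correlation, and give a range over ICC and club size.

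**Cost.** Revised analysis wording, one variable, and somewhat wider confidence intervals for Arm 1. Trial status gives enrolment as complete, and no change to it is needed. If the ICC proves negligible, little precision is lost.

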### Primary and secondary outcomes

For Aim 1, our primary outcome will be the proportion of eligible individuals accepting PrEP as part of CBCT services. Secondary outcomes will include (1) stratification of PrEP initiation by both location and CBCT platform; (2) in-depth qualitative understanding of PrEP initiation; (3) correlates of immediate, delayed, and no PrEP initiation; and (4) comparison of sexual behaviours, risk profiles, and self-perception of risk in immediate, delayed, and never acceptors. Using the IMB model to inform the selection of variables and contextualization of results, an assessment of determinants of PrEP uptake will include (1) socio-demographic factors, (2) risk behaviours, (3) self-perception of risk, (4) previous knowledge of PrEP and perception of those taking PrEP, (5) partner characteristics and HIV status, (6) HIV-related stigma, and (7) screening scores for depression, substance abuse, and social support. Baseline STIs will be used as an independent marker of sexual risk behaviour, and to validate self-reported sexual risk behaviours and self-perception of risk.

For Aim 2, the primary outcome will be a comparison of TFV-DP levels by study arm at months 3, 6, 12, 18, and 24, with a 12-month primary outcome and 24-month assessment of intervention durability. Based on cumulative adherence behaviour, as measured in iPrEX OLE [14], adherence will be categorized as (1) *low adherence* (≤ 3 tablets per week; ≤ 699 fmol/DBS punch), and (2) *high adherence* (4–7 tablets per week; ≥ 700 fmol/DBS punch). Analysis of primary outcomes will be conducted on an intention-to-treat basis. Secondary outcomes will include (1) predictors of PrEP adherence after adjusting for study arm, socio-demographic factors, exposure to adherence support activities, and risk profiles; (2) characterization of changes in sexual behaviours and risk profiles following PrEP initiation; (3) proportion of individuals who discontinue PrEP and factors associated with discontinuation; (4) proportion of individuals who discontinue but subsequently restart PrEP and characteristics associated with this subgroup; (5) factors associated with of patterns of PrEP use; and (6) profiles of individuals that may benefit more from group-based vs. individualized adherence support.

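### The longitudinal model's stated fixed effects, time and intervention with no arm-by-visit term, do not match the month-12 primary outcome or the month-24 durability assessment

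*Protocol article*

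**What the plan says.** Primary and secondary outcomes gives the Aim 2 primary outcome in these words: "comparison of TFV-DP levels by study arm at months 3, 6, 12, 18, and 24, with a 12-month primary outcome and 24-month assessment". The month-24 part concerns durability. Table 1 (Aim 2) gives the same two targets. Table 2 and the Tenofovir testing section schedule the drug-level measurement at those five visits, with none at baseline.

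Three statements in Data analysis bear on how these targets would be estimated:

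- For repeated measurements, the stated purpose is general: "Generalized linear mixed effect models will be fitted to determine associations of interest". The terms of these models are then listed as follows: "with time and intervention effects included as fixed effects and allowing for subject-specific random effects".
- Generalized estimating equations are offered as an alternative "when assessing determinants of PrEP adherence at time points provided we have balanced data with ignorable missing patterns".
- The primary analysis is to assume data missing at random, and for that reason "longitudinal likelihood-based data analysis, utilizing all the observed pre-deviation data from each participant will be employed".

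A cross-sectional test appears in two places. Sample size and power calculations sizes Aim 2 "using the chi-square test for independence with two degrees of freedom, with an alpha of 0.05". Data analysis says, next to the description of participant characteristics, "The chi-squared statistic test will be used for categorical variables". Neither place says which method yields the month-12 primary result.

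**The concern.** The article sets two targets tied to particular visits: the arm difference at month 12 and the arm difference at month 24. Asking about durability presumes that the effect may change between visits. A model whose fixed effects are time and intervention lets the overall adherence level move over time but gives each intervention arm a single coefficient against control. That coefficient applies equally to all five visits. All five are after randomization, so it pools the whole period from month 3 to month 24.

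Two errors could follow. An early effect that has gone by month 12 would still show as a positive arm effect. A real month-12 effect that later fades would be diluted at month 12 and carried forward to month 24 as if it had lasted.

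**Working it through.** **1. The plan's own figure.** Inputs from Sample size and power calculations: effect size 0.15, alpha 0.05, power 80%, chi-square with 2 df, attrition 10%, 160 per arm. Reading 0.15 as Cohen's w, the noncentral chi-square with noncentrality N × 0.15² gives N = 428.2, so 429 evaluable. Then 429 / 0.90 = 476.7, so 477 (159 per arm) against 480 stated. With 480 × 0.90 = 432 completers, power is 80.4%. The stated size is reproduced and is not in dispute. It belongs to one cross-sectional comparison, not to the longitudinal model.

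**2. What the model estimates as written.** With the listed terms:

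g(E[Y at visit v]) = intercept + time(v) + arm effect + subject effect.

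The arm effect carries no index v. In a balanced linear model its estimate is the plain mean of the five visit-specific differences. With a logit link or missed visits it is a weighted, subject-specific quantity, but still one number for all visits.

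**3. Illustration of size.** The assumptions here are not in the article: linear model, complete data, adherence near 50%, one intervention arm against control, within-subject correlation rho of 0.3 to 0.7, and a 16-point difference. The 16 points come from w = 0.15 with both intervention arms equally above control and rates near 50%: 2d²/9 = 0.15² × 0.25, so d = 0.159. Per arm, n = 160 × 0.90 = 144.

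- Differences 16/16/0/0/0: pooled estimate (16 + 16) / 5 = 6.4 points; true month-12 difference 0.
- Differences 16/16/16/0/0: pooled estimate (3 × 16) / 5 = 9.6 points. That is 40% too small at month 12 (6.4 / 16) and 9.6 points too large at month 24.

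Standard error of the pooled difference = sqrt(2 × 0.25 × (1 + 4 × rho) / 5 / 144). For the first pattern, two-sided 5% test:

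| rho | SE | 0.064 / SE | Rejection |
|---|---|---|---|
| 0.3 | 0.0391 | 1.64 | 37% |
| 0.5 | 0.0456 | 1.40 | 29% |
| 0.7 | 0.0514 | 1.25 | 24% |

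**4. Check with other patterns.** One simulated data set per pattern was used: 4,000 per arm, control adherence 30% at every visit, complete data. It was analysed by generalized estimating equations with identity link and exchangeable correlation. Figures are percentage points.

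| True difference at months 3/6/12/18/24 | Without interaction | With interaction, month 12 | With interaction, month 24 |
|---|---|---|---|
| 25/20/15/5/0 | 12.8 | 13.3 | -0.5 |
| 30/20/5/0/0 | 11.1 | 5.4 | -1.0 |
| 0/5/15/20/25 | 12.7 | 15.4 | 23.9 |
| 15 throughout | 14.5 | 15.5 | 14.2 |

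Where the effect varied, the single estimate missed the true month-12 difference by about 2 to 6 points and the true month-24 difference by about 11 to 13. With a constant effect the two models agree within simulation error.

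**The case against.** The strongest reply has four parts.

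*The text never says main effects only.* This is correct. The phrase separates fixed from random terms and rules out no interaction. A reader might infer that the trial has committed itself to a main-effects model; the article does not support that. A condensed article may also leave model terms to the full protocol, which the Data Availability section says exists. What stands against this is that the article did choose to list the fixed effects, and the list given does not fit the outcome given.

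*The plan can reach month 12 without this model.* A reader might infer that the plan cannot deliver its primary contrast at all. That goes too far, because a chi-square test on the month-12 adherence categories would give a month-12 comparison. However, the article does not name that test as the primary one. It is also not the longitudinal likelihood analysis of all observed data that Data analysis calls for.

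*The mixed model is for associations, not for the primary test.* Its stated purpose is indeed general. But it is the only longitudinal likelihood model the article describes for repeated adherence data, and the primary analysis is assigned to that class.

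*The magnitudes are assumed.* This is accepted. The effect patterns, rates and correlations are not document figures. Sessions are planned monthly for all 24 months, so a full effect falling to exactly zero is an extreme case. The 16 points depend on reading 0.15 as Cohen's w with two equal intervention arms; equally spaced arms would give an extreme difference of about 18 points. The averages are exact only for a balanced linear model, not for the generalized mixed model named.

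**Conclusion.** The point holds as a mismatch between a stated model and stated targets. As written, the longitudinal model imposes one arm effect, on the link scale, across months 3 to 24. It neither isolates month 12 nor assesses durability. The article does not establish that an interaction will be left out, nor that no month-12 test is available.

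The size depends on how the effect moves over time, which is unknown. If it is constant, nothing is lost. Under the front-loaded illustration, about 6.4 points would be reported, with 24% to 37% rejection, when the month-12 effect is zero. Because the point concerns the primary result, it should be fixed before arm-level outcomes are analysed. Confidence is moderate, given that an interaction is not excluded and the chi-square route is open.

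**What to change.** Specify visit as a categorical factor with an arm-by-visit interaction in the longitudinal model. Take the month-12 arm contrasts from it as the primary result and the month-24 contrasts as the durability estimate, both expressed as marginal risk differences. If a month-12-only chi-square test is meant to be primary, say so and use the interaction model for durability.

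The cost is one added model term and a sentence naming the contrasts. The month-12 interval will be wider than that of a pooled effect. In the balanced illustration the month-12 standard error is sqrt(2 × 0.25 / 144) = 0.0589 against 0.0391 to 0.0514 pooled, so the interval is about 1.5 times as wide at rho 0.3 and 1.15 times at rho 0.7. The gain is that it estimates the outcome the article states. The sample size need not change: with complete data the month-12 comparison is the one for which 480 was calculated.

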**Special study activities***											
**ACASI Questionnaire**	**X**			**X**			**X**				**X**
**CrCl testing**	**X**			**X**			**X**				**X**
**STI testing**	**X**				**X**		**X**				**X**
**Blood testing for detectable TFV-DP**				**X**	**X**		**X**		**X**		**X**
**Hepatitis B testing and vaccination**	**X**	**X**			**X**						

* A R30.00 (~$2.00) voucher will be provided after each “special” study visit where specimens are collected (i.e. M3, 6, 12, 18, and 24)

Monthly activities will include (1) attendance check-in, (2) adherence support session (intervention arms only), (3) clinical assessment, (4) medication dispensing, (5) study visit reminders, and (6) study pack and voucher. Each month, study staff will contact participants up to three times via SMS and phone calls as study visit reminders to support retention. More details about intervention and control arms is available in Table 3.

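### The optional as-treated analysis of an adherence outcome would favour the intervention if missed sessions count as non-adherence, and an adherence-marker covariate can dilute a true arm effect

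*Protocol article*

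**What the plan says.** Under Primary and secondary outcomes, the Aim 2 endpoint is drug concentration: "the primary outcome will be a comparison of TFV-DP levels by study arm at months 3, 6, 12, 18, and 24", with month 12 primary. High adherence is defined as "4–7 tablets per week; ≥ 700 fmol/DBS punch". The analysis set is fixed there: "Analysis of primary outcomes will be conducted on an intention-to-treat basis".

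The Data analysis section returns to the subject in three sentences:

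- On the analysis set, it says: "Intention to treat (ITT) assessment with complete case approaches where necessary will be implemented in cases of non-adherence to randomization assignment".
- On an alternative, to be chosen according to how much of this is seen, it says that as-treated "approaches may be employed to analyse participants according to the intervention received regardless to their randomized allocation".
- On covariates, it says: "A marker of level of adherence can also be included in the models".

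The list of monthly activities below Table 2 puts support and drug supply in one visit: "2) adherence support session (intervention arms only), (3) clinical assessment, (4) medication dispensing". The Control section has control women returning monthly for refills without a session, and the enrolment section gives each woman 30 days of drug at the start. Table 4 treats sessions and medication collection as one event when it defines women who never came back.

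**The concern.** In most trials an as-treated analysis is weak because people who take up an intervention differ from those who do not. Here the link is closer. A woman in an intervention arm who misses her session has probably also missed her refill, so her TFV-DP is likely to be low whatever the session would have done. If she is reclassified as not having received the intervention, she joins the comparator and lowers its adherence rate. Control women who miss visits are in the comparator under either scheme, so nothing offsets the shift. The bias grows with non-attendance, and the extent of non-adherence is also what the plan names as the reason to use the method. The Discussion expects that consistent health-club attendance may be hard to achieve.

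At stake is a favourable secondary result, not marked as supportive, that could be reported beside a null ITT result.

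The adherence marker is a separate problem. In an arm comparison it is measured after randomisation, and it is either a step on the path from support to TFV-DP or a proxy for TFV-DP itself.

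**Working it through.** **The plan's own figure.** The article states 160 per arm (480 in all) for a chi-square test with 2 degrees of freedom, alpha 0.05, 80% power, effect size 0.15 (read as Cohen's w) and 10% attrition. The required non-centrality is 9.635. N = 9.635 / 0.15² = 428.2, so 429. 429 / 0.9 = 476.7, so 477, or 159 per arm. This agrees with 480. The checks below use 160 × 0.9 = 144 per arm.

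**As-treated with no true effect.** Let a be the share of every arm that attends and collects drug, h1 the proportion with high adherence among attenders, and h0 that among non-attenders, all equal across arms. These three inputs are assumptions; the documents give none of them.

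- ITT: each arm has a·h1 + (1−a)·h0, so the difference is 0.
- As-treated: the received groups have h1. The comparator holds the control arm plus the non-attenders of two intervention arms, of relative size 1 + 2(1−a) = 3 − 2a. Its proportion is [a·h1 + 3(1−a)·h0] / (3 − 2a).
- Spurious difference = 3(1−a)(h1−h0) / (3 − 2a).

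At a = 0.8 the multiplier is 3 × 0.2 / 1.4 = 0.4286. It gives 0.4286 × 0.10 = 4.3 points, 0.4286 × 0.30 = 12.9 points and 0.4286 × 0.50 = 21.4 points.

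The table adds the false-positive rate of the chi-square test with 2 degrees of freedom, from 2,000 simulated trials per cell:

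| Attendance | 30% v 20% high | 30% v 0% high | 50% v 0% high |
|---|---|---|---|
| 90% | +2.5 points, 7% | +7.5 points, 33% | +12.5 points, 62% |
| 80% | +4.3 points, 14% | +12.9 points, 83% | +21.4 points, 99% |
| 70% | +5.6 points, 20% | +16.9 points, 99% | +28.1 points, 100% |
| 50% | +7.5 points, 33% | +22.5 points, 100% | +37.5 points, 100% |

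ITT rejected in 4.5% to 6.4% of trials across all scenarios, which is 5% within simulation error. With h1 = h0 the as-treated bias is zero.

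**Non-attenders without a sample.** If intervention non-attenders drop out rather than move, and control non-attenders are still measured, the bias is (1−a)(h1−h0). At 80% attendance and 30% v 0% this is 0.2 × 0.30 = 6.0 points, with 18% false positives. If non-attenders in every arm have no sample, the comparison is h1 against h1 and the bias vanishes under these assumptions.

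**Adherence marker.** Take two arms of 144, with the outcome and the marker each equal to latent adherence plus independent noise, and marker reliability r. The coefficient of the marker is r, so the adjusted arm effect is the true effect × (1 − r). For a true effect of 0.30 latent SD, 0.30 × 0.7 = 0.21, 0.30 × 0.5 = 0.15 and 0.30 × 0.2 = 0.06 at r = 0.3, 0.5 and 0.8. Simulation (1,000 runs each) gave the same values. Power fell from 31%, 45% and 64% unadjusted to 19%, 17% and 10% adjusted. With no true effect the adjusted test rejected about 5% of the time.

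**The case against.** Five points can be made for the plan.

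1. **ITT is already the primary basis.** This stands. The as-treated sentence is permissive, nothing lets it replace ITT, and the error rate of the confirmatory test is untouched. A reader might infer that the plan can switch its main analysis to as-treated; the documents do not say that.
2. **Non-adherence to assignment may mean crossover rather than missed sessions.** This stands as a limit. The text does not settle it. A woman who swaps between group and individual support still attends and collects drug, so this mechanism does not arise for her.
3. **A missed session need not mean no drug.** This stands in part. Session and dispensing are separate items, controls collect drug without a session, and clubs are to be flexibly scheduled. Overlap is likely but not shown to be complete, which is why the table includes a gap of only 10 points.
4. **The marker may be meant for secondary models.** This is possible. The predictor analysis, which adjusts for exposure to support, is a proper place for it. A reader might also infer that marker adjustment manufactures an effect. The case tested shows the opposite, although bias in either direction is possible if marker and outcome share unmeasured causes or the marker works differently by arm.
5. **Definitions belong in the analysis plan.** This is fair for what counts as received and which marker is used, and their absence here is not a fault. What the article does state is a choice of method that depends on the observed extent of non-adherence, and that can be judged as it stands.

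**Conclusion.** The concern holds in a limited, conditional form. The confirmatory ITT comparison is sound and the sample size is unaffected. The weakness lies in the additional analyses: an as-treated comparison invoked according to the data and not marked supportive, for an outcome tied to attendance by the visit structure.

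If missed sessions count as non-adherence and non-attenders are measured and moved to the comparator, the bias favours the intervention whenever attenders have higher TFV-DP. At 80% attendance it runs from about +4 to +21 points over the assumed adherence gaps. It is smaller if non-attenders have no sample. None of these figures predicts this trial.

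Marker adjustment of an arm comparison is a separate fault, and in the case tested it acts towards the null.

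A reader might also infer that the complete-case clause should be deleted. This check does not support that: the same section sets a likelihood-based primary analysis under missing at random, then multiple imputation and sensitivity analyses.

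**What to change.** Three changes of wording:

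1. State that ITT on all randomised women is the only confirmatory arm comparison. This also removes any impression from "with complete case approaches where necessary will be implemented in cases of non-adherence to randomization assignment" that ITT applies only when non-adherence occurs.
2. Replace the discretionary as-treated option with one pre-named secondary analysis: a complier average causal effect for each intervention arm against control, with randomisation as instrument and sessions attended as exposure. Sessions are offered in the intervention arms only, so non-compliance is essentially one-sided. With attendance as a yes/no exposure, the estimate is the ITT difference divided by the attendance share. Under no effect and 80% attendance that is 0 / 0.8 = 0, where as-treated gave up to +21 points.
3. Keep post-randomisation adherence markers out of arm-comparison models, except in an analysis labelled as mediation or as a study of predictors.

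The cost is analysis-plan wording, with no new data and no change to the 480. The complier estimate has a wider interval than an as-treated one, and it assumes that allocation affects TFV-DP only through the sessions attended.
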